## Abstract

**Background:**

Vulvar lichen planus (VLP) is a chronic vulvar dermatosis that is difficult to treat and can severely impair quality of life in the absence of adequate treatment. There is a lack of high-quality evidence to direct therapy for VLP. This randomised controlled trial will be the first double-blinded study comparing systemic treatments in VLP and aims to investigate the safety and efficacy of deucravacitinib compared to methotrexate, in patients with VLP who have failed treatment with potent topical corticosteroids.

**Methods:**

A total of 116 women aged ≥ 18 years with moderate to severe VLP (Genital Erosive Lichen Planus (GELP) score ≥ 5) will be recruited. All participants will initially be treated with Diprosone® OV daily, and their outcome will be assessed using the GELP score. At 8 weeks’ follow-up, responders (GELP < 5) will be continued on Diprosone® OV. Non-responders (GELP ≥ 5) will be randomised 1:1 in a blinded fashion to receive (i) methotrexate 10 mg weekly + placebo tablet twice daily + folic acid 5 mg weekly or (ii) deucravacitinib 6 mg twice daily + placebo tablet weekly + folic acid 5 mg weekly. The primary endpoint is the difference in the mean change of GELP scores from baseline to week 32 between deucravacitinib and methotrexate groups.

**Discussion:**

High-quality evidence guiding the management of women with VLP is lacking. Once completed, this will be the first double-blinded RCT to compare systemic treatments in VLP. The results of this study will provide valuable, high-quality data to guide second-line therapy options for VLP that is recalcitrant to potent topical corticosteroids.

**Trial registration:**

Australian New Zealand Clinical Trials Registry ACTRN12623000682640. Registered on 26 June 2023.

## Administrative information

Note: the numbers in curly brackets in this protocol refer to the SPIRIT checklist item numbers. The order of the items has been modified to group similar items (see http://www.equator-network.org/reporting-guidelines/spirit-2013-statement-defining-standard-protocol-items-for-clinical-trials/).

## Introduction

### Background and rationale {6a}

Since the 1900s, women’s health has been recognised as an important public health issue. Australia’s first National Women’s Health Policy was created in 1989, with one of the underpinning principles being “a lifespan approach without undue focus on the reproductive years” [1]. The listed priority areas included reproductive health and sexuality, mental and emotional health, and the health of ageing women. This reflected public awareness that women’s health requires a holistic approach and has changing needs throughout the stages of life.

Since then, considerable progress has been made in women’s health, such as access to contraception, access to regular cervical screening testing, mammography and in vitro fertilisation.

Importantly, the Australian National Women’s Health Strategy 2020–2030 reported it is paramount that we “identify and focus on the collection of more detailed and nuanced data, particularly for women and girls in underrepresented population groups and with less prevalent conditions, to inform health policy development and program delivery and to break the ‘cycle of invisibility’” [2].

Unfortunately, diseases affecting the genitals remain ‘invisible’ and an unmet need. This is despite genital diseases having one of the greatest influences on quality of life; genital diseases have substantial impacts on self-esteem, psychological well-being, physical activities, influence body image, clothing choices, disturb sleep, impair activities of daily living, leisure activities, the ability to work and relationships and sexual function [3–5].

Genital diseases are often overlooked in clinical practice, either due to reticence by patients to bring their embarrassing condition to attention, or clinicians, who feel ill-equipped to address them. Patients often present many years after suffering silently and, when they do, are often screened for sexually transmitted infections, repeatedly. Patients remain invisible and alone.

Vulvar lichen planus (VLP), the disease in focus in the presented study protocol, is a chronic inflammatory dermatosis characterised by erythema, erosions and hyperkeratosis on the vulva with possible vaginal involvement [6, 7]. It has a predilection for peri-/post-menopausal women in the fifth to sixth decades of life [8, 9]. The exact prevalence of VLP is unknown. It is estimated to be 3.7% from a study of 3350 women presenting to a vulvar clinic [8]. However, the actual prevalence in the general population is likely to be higher due to underdiagnosis.

Patients report significant vulvar pruritus, pain, burning sensation, discharge and dyspareunia, which leads to debilitating effects on sexual function and other aspects of life and reduces quality of life [4, 10, 11]. Ongoing disease activity can lead to vulvovaginal scarring and malignancy [10–12].

VLP is particularly difficult to treat. Unfortunately, despite the recognised disease sequelae and impact on quality of life, there are limited studies on direct therapy for VLP. The first-line treatment for VLP is potent topical corticosteroids, but approximately 20–40% of patients require second-line treatment with systemic immunosuppression to control their disease [9, 13]. Some of the systemic medications that have been used to treat VLP include prednisolone, methotrexate, mycophenolate mofetil, azathioprine, hydroxychloroquine, cyclosporine, rituximab, tildrakizumab, secukinumab, ustekinumab, adalimumab, tofacitinib and apremilast with varying results [14–26]. The best-documented agent appears to be methotrexate, with authors reporting a moderate efficacy and safety profile [15, 27–29]. However, these studies were either retrospective or small case series. There is no high-quality evidence, such as RCTs, to compare and guide second-line systemic treatments in VLP.

The pathogenesis of VLP is not completely understood, but there is evidence of involvement of tyrosine kinase 2 (TYK2)-mediated pathway. Cytokines, such as interleukin (IL)-12, IL-23 and type 1 interferon (IFN), signal through TYK-2, promoting the release of effector cytokines such as IL-17, which is known to play a role in the pathogenesis of various immune-mediated diseases [30]. IL-12/23 inhibitor ustekinumab and IL-23 inhibitor guselkumab have shown promise in the treatment of lichen planus, and tildrakizumab, an IL-23 inhibitor, was recently reported in the successful treatment of 24 women with VLP [19, 21]. Rapid clinical improvement and a marked decrease in IL-17A expression were demonstrated in a patient with VLP following a 12-week treatment with secukinumab, an IL-17A inhibitor [21].

One drug known to modulate the TYK-2 pathway is deucravacitinib (Sotyktu), a novel, first-in-class, oral, selective, allosteric TYK-2 inhibitor. It has been approved in Australia for adult patients with moderate-to-severe plaque psoriasis who are candidates for systemic therapy or phototherapy, and is being studied in psoriatic arthritis, alopecia areata and systemic lupus erythematosus with promising results [31–34].

### Objectives {7}

Given the lack of high-quality evidence to guide the use of second-line systemic treatments in VLP, the evidence of involvement of TYK2-mediated pathway in VLP and that the best documented systemic agent in VLP to date is methotrexate, the aim of this study is to conduct a double-blinded RCT comparing the efficacy and safety of deucravacitinib to that of methotrexate, in patients with VLP who have failed first-line treatment with potent topical corticosteroids. Once completed, this will be the first double-blinded RCT comparing systemic treatments in VLP. The results of this study will guide the management of patients with this chronic, long-neglected and particularly difficult-to-treat condition, addressing what is currently an unmet need.

### Trial design {8}

This study is a double-blinded, single-centre RCT with a parallel group design. The trial will take place over 36 weeks. Recruited participants will be prescribed potent topical corticosteroids with Diprosone® OV (betamethasone dipropionate 0.05% ointment in optimised vehicle) daily. At 8 weeks’ follow-up, those who have not responded to Diprosone® OV, defined by a Genital Erosive Lichen Planus (GELP) score [7] ≥ 5, will be randomised in a 1:1 ratio and blinded fashion to either the methotrexate or deucravacitinib group. The treatment will conclude at week 32. There will be a follow-up visit 30 days following the end of the treatment period.

## Methods: participants, interventions and outcomes

### Study setting {9}

This RCT will be undertaken at dermato-gynaecology clinic rooms of dermatologists who specialise in disorders of the vulva in Sydney, Australia.

### Eligibility criteria {10}

The inclusion criteria are females aged ≥ 18 with a diagnosis of moderate-to-severe VLP, demonstrated by a GELP score ≥ 5, of which erythema and pain must score ≥ 1. The diagnosis needs to be confirmed by either histopathology or fulfilling diagnostic criteria developed by Wu et al. [6] or Simpson et al. [35].

The exclusion criteria are:Those with a lichen sclerosus/lichen planus overlap.Patients receiving other systemic immune-modulating therapy within the previous 4 weeks.Has cancer or a history of cancer (solid organ, hematologic including myelodysplastic syndrome or melanoma in situ) or lymphoproliferative disease within the previous 5 years (other than resected cutaneous basal cell or squamous cell carcinoma, or carcinoma of the cervix in situ that has been treated with no evidence of recurrence).Premalignant cervical or vulvar disease.Live vaccine administration within the last 4 weeks.The concomitant use of strong CYP3A4 enzyme inducers.Inadequate birth control (if pre-menopausal), pregnancy, planning pregnancy during the study period and/or breast-feeding.A past medical history of depression and/or suicidal ideation. If these are reported on screening questions, then the subject will undergo a Patient Health Questionnaire 8 items (PHQ-8) excluding those when the total score is ≥ 15.Patients with severe renal/liver impairment or concurrent medications that would interact with the trial medications.Patients with active tuberculosis (TB), including any symptoms or signs, or imaging showing active TB, or latent TB determined by a positive IFN-gamma release assay and including current treatment for latent TB.Patients with other serious infections, defined by evidence of active infection or febrile illness within 7 days prior to day 1; a history of serious bacterial, fungal, or viral infection requiring hospitalization and/or intravenous antimicrobial intervention within 60 days prior to day 1; any ongoing evidence of chronic, bacterial infection (e.g. chronic pyelonephritis, chronic osteomyelitis, chronic bronchiectasis); a history of prosthetic joint infection where the prosthesis was not removed; active herpes simplex virus or herpes zoster infection at day 1; positive test for hepatitis B virus (positive HBsAg, HBcAb); evidence of, or test positive for, hepatitis C virus (HCV) at screening (anti-HCVAb), positive for human immunodeficiency virus by antibody testing (HIV-1 and HIV-2 Ab).Any history of known or suspected congenital or acquired immunodeficiency state or condition that would compromise the participant’s immune status (e.g. history of opportunistic infections [e.g. *Pneumocystis jirovecii* pneumonia, histoplasmosis, or coccidioidomycosis], history of splenectomy, primary immunodeficiency).Severe SARS-CoV-2 infection (e.g. worsened shortness of breath and pneumonia) within 4 weeks prior to screening. Additionally, in the case of prior SARS-CoV-2 infection, symptoms must have completely resolved, and based on investigator assessment in consultation with the clinical trial physician, there are no sequelae that would place the participant at a higher risk of receiving investigational intervention.Any history of hypersensitivity to the active substance(s) or to any of the excipients of deucravacitinib or methotrexate.Participation in another trial that could affect the current study.

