### Criteria for discontinuing or modifying allocated interventions {11b}

A participant may withdraw from the study for any reason at any time.

Permanent discontinuation from the study will take place if a participant:Requires oral corticosteroids for more than four consecutive weeks.Requires rescue treatment with a non-corticosteroid systemic agent (including but not limited to cyclosporine, methotrexate, mycophenolate mofetil, or azathioprine) or injectable or parenteral corticosteroid.Develops clinically significant abnormal laboratory results or adverse events (AEs), which rule out continuation of the study drug, as determined by the investigator.Becomes pregnant or plans to become pregnant during the study.Develops active TB during the study.Develops malignancy, except for localised non-melanoma skin cancers or carcinoma of the cervix in situ.Has a confirmed diagnosis of deep vein thrombosis, pulmonary embolus, or non-cardiac, non-neurologic arterial thrombosis.Takes prohibited medications when the continuation of the study drug would place the subject at risk, as determined by the investigator.Significantly non-compliant with study procedures, which would put the participant at risk for continued participation in the trial as determined by the investigator.

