### Procedure for unblinding if needed {17b}

Unblinding of the treatment allocation will be allowed in events such as medical emergencies, where the safety and well-being of the participant are of concern. The pharmacy will be contacted to assist with unblinding.

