### Composition of the data monitoring committee, its role and reporting structure {21a}

There will not be a separate data monitoring committee. However, an independent Medical Monitor will be appointed.

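### The depression and suicidal ideation criterion turns only on a PHQ-8 total of 15 or more, so reported current ideation has no weight of its own at entry

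*Protocol article*

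**What the plan says.** In the protocol article, Eligibility criteria {10}, the exclusion list includes this item: "A past medical history of depression and/or suicidal ideation. If these are reported on screening questions". The sentence then continues: "then the subject will undergo a Patient Health Questionnaire 8 items (PHQ-8) excluding those when the total score is ≥ 15". The item gives no time window for the history and no separate rule for ideation that is present at screening.

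Other items in the same list do handle timing or clinical judgement. For infection there is a look-back window, "a history of serious bacterial, fungal, or viral infection requiring hospitalization and/or intravenous antimicrobial intervention within 60 days prior to day 1", and a present-state rule, "active herpes simplex virus or herpes zoster infection at day 1". For earlier SARS-CoV-2 infection, entry depends on a clinical judgement: "based on investigator assessment in consultation with the clinical trial physician, there are no sequelae that would place the participant at a higher risk".

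After entry, four general provisions apply:
- a discontinuation reason covering "adverse events (AEs), which rule out continuation of the study drug, as determined by the investigator" (section {11b});
- the unblinding procedure: "Unblinding of the treatment allocation will be allowed in events such as medical emergencies" (section {17b});
- in place of a data monitoring committee, "an independent Medical Monitor will be appointed" (section {21a});
- investigator monitoring for adverse events throughout the study (section {22}).

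**The concern.** The item names suicidal ideation as a reason for concern at entry, but what excludes is a total score on a depression questionnaire. A positive answer on ideation serves only to start the questionnaire. Once the total is known, the answer plays no further part in this criterion, whether the ideation lies years back or is present on the day of screening.

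What is at stake is participant safety at entry. The sponsor chose to ask about ideation, so it judged the answer relevant to eligibility. The article's own background also says that genital disease affects psychological well-being, so some positive answers are foreseeable. An entry rule should say what happens when the answer is the serious one.

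**Working it through.** There is no stated figure to reproduce and no formula applies. The check is to apply the text to each kind of participant and then look for another rule that would catch the case of interest.

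**Step 1: how the two sentences fit together.** The second sentence is conditional on what the first one names, so it is the operating rule for the first. If history alone excluded, a questionnaire with a cut-off for exactly those women would serve no purpose. The rule is therefore: history reported, PHQ-8 given, exclusion at a total of 15 or more.

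**Step 2: apply the rule.**

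| Reported at screening | PHQ-8 total | Result under this criterion |
|---|---|---|
| Depression, no ideation | below 15 | passes |
| Remote suicidal ideation | below 15 | passes |
| Current suicidal ideation | below 15 | passes |
| Any of the above | 15 or more | excluded |

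The first three rows end the same way. For the first two this is reasonable, since an old or resolved history need not bar entry. The third row is the problem.

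**Step 3: is the third row caught by another entry rule?** The exclusion list has 15 items:
1. lichen sclerosus overlap
2. other systemic immune-modulating therapy
3. cancer
4. premalignant disease
5. live vaccine
6. CYP3A4 inducers
7. contraception and pregnancy
8. depression and/or suicidal ideation
9. renal or liver impairment or interacting drugs
10. tuberculosis
11. other serious infections
12. immunodeficiency
13. SARS-CoV-2
14. hypersensitivity
15. another trial

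Only item 8 names ideation, which leaves 15 − 1 = 14 that do not. The inclusion criteria concern sex, age, diagnosis and GELP score.

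**Step 4: is it caught later?** Section {11b} gives 9 reasons for permanent discontinuation, and 0 of them name suicidal ideation. The adverse-event clause there, emergency unblinding, the Medical Monitor and adverse-event monitoring could all respond to a deterioration. They are general, and they act once the woman is already in the trial. They do not decide who enters.

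**Step 5: could the protocol have written it otherwise?** Yes. The infection item already distinguishes a past event from an active one, and the SARS-CoV-2 item already relies on an investigator's assessment. A rule of the same kind for ideation would be in keeping with the list.

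**The case against.** The strongest reply has four parts.

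- **The rule is complete and deliberate.** History does not bar entry; a score taken at screening does. Relying on a total score and not on a separate ideation rule is a choice of instrument. It stands that the rule is usable as written. It does not follow that the result is the best one: the criterion names ideation and then gives it no effect of its own.
- **The screening questions are not shown.** The item is worded as past history, and the article condenses a protocol (v1.3) that may say how a positive answer is handled. This stands as a condition on the point: it bites for current ideation only if the questions elicit it. It does not remove the point, because the article states trigger, instrument and cut-off, and so fixes a rule with that consequence.
- **The list has no uniform convention on timing.** The immunodeficiency and hypersensitivity items also take any history without a past/current split. This is true, and the infection and SARS-CoV-2 items are used here only to show that such a rule is feasible. Those two history items also differ in that they exclude outright.
- **The counts measure no harm.** This is also true. One item in 15 and none in 9 show where the text is silent, not how many women are affected.

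A reader might infer more: that the two sentences contradict each other, so that two screeners could decide the same woman differently. The documents do not support that. It requires reading the first sentence while ignoring the one that says how it operates. What remains is untidy wording, since an item placed under the exclusions never says that history alone does not exclude.

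**Conclusion.** The point holds as a limited matter of participant safety at entry. The criterion works as a two-step screen with one deciding number. Under it, a woman with current suicidal ideation and a PHQ-8 total below 15 passes, and no other entry criterion addresses her case.

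This rests on two assumptions: that the screening questions elicit current ideation, and that no unseen entry rule in the full protocol deals with it. Passing this criterion also does not mean that she would be enrolled, since the other criteria still apply.

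The size cannot be given. The article reports no frequency of ideation or of PHQ-8 totals in this population, so no number of women is claimed. A reader might also infer that one of the study drugs carries a suicidality risk; nothing in the article says so, and the point does not need it. Sample size, power, the primary endpoint and the primary analysis are unaffected. The change is worth making because it is cheap and protects participants, not because the trial's result depends on it.

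**What to change.** Replace the two sentences with one rule, for example:

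> Depression or suicidal ideation reported at screening, past or present, does not exclude by itself. It leads to a PHQ-8 and a documented assessment by the investigator. A woman is excluded if her PHQ-8 total is 15 or more, or if the assessment finds current suicidal ideation at screening, whatever the total.

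This keeps the existing trigger and cut-off, does not bar women with a remote history, and settles the wording of the first sentence. The protocol should also make sure that the screening questions ask about present ideation, so that the rule has something to act on.

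The cost is one short amendment to the text, a brief recorded assessment limited to women already flagged, and possibly a few more screen failures. No change to the sample size or the analysis follows from it.

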
### Who will take informed consent? {26a}

The recruiting investigators will obtain written informed consent from all eligible and interested participants prior to conducting any trial-related procedures. The investigators will ensure that participants are clearly and fully informed about the purpose, potential risks, alternative treatments available and other important matters regarding the clinical trial.

### Additional consent provisions for collection and use of participant data and biological specimens {26b}

There will be a separate consent form for tissue sampling in matched healthy controls for biomarker assessments.

## Interventions

### Explanation for the choice of comparators {6b}

Methotrexate was chosen as the comparator, as this is the best-documented agent for VLP [15, 27–29]. It is worth noting however that these studies were either retrospective or small case series, emphasising the scarcity of high-quality studies in VLP.

### Intervention description {11a}

All participants will initially be prescribed potent topical corticosteroids with Diprosone® OV daily. At 8 weeks’ assessment, responders (GELP < 5) will be continued on Diprosone® OV. Non-responders (GELP ≥ 5) will be randomised 1:1 in a blinded fashion to:Oral methotrexate 10 mg weekly + oral placebo twice daily + oral folic acid 5 mg weekly, OROral deucravacitinib 6 mg twice daily + oral placebo weekly + oral folic acid 5 mg weekly.

The treatments will be continued until week 32.

